## Abstract

The current state of knowledge related to diet in Hashimoto thyroiditis (HT) is far from satisfactory, as many HT subjects experience several disorders and report reduced quality of life. There are three aims of the study: (1) to develop a qualitative dietary protocol (QDP; ‘Diet4Hashi’) as a simple, graphic–text tool dedicated to TH subjects, (2) to evaluate the use of the QDP in dietetic counseling compared to conventional dietetic counseling (CDC) in HT women, and (3) to assess the impact of both the QDP and the CDC on the diet quality, quality of life, adiposity, and metabolic parameters of HT women. The QDP is based on subject self-monitoring supported with a graphic–text tool to help them in food selection and adequate food frequency consumption, while the CDC on oral explanation and printed sample menus were provided by a dietician. The QDP contains two lists: (A) foods recommended for consumption and (B) foods with limited consumption, along with indicated consumption frequency per day/week/month. Both approaches include the same dietary recommendations for HT extracted from the literature but differ in subject–dietician cooperation. To summarize the evidence regarding dietary recommendations in HT, the PubMed, Embase, and Cochrane Library databases (to March 2019) and the bibliographies of key articles were searched. The study is designed as a dietary intervention lasting six months in two parallel groups: experimental and control. In the experimental group, the QDP will be applied, while in the control group, the CDC will be applied. In total, the study will include a baseline of 100 women with diagnosed HT. The subjects will be randomly allocated into the experimental/control groups (50/50). Data related to diet quality and other lifestyle factors, nutrition knowledge, quality of life, thyroid function, body composition, blood pressure, serum fasting glucose, and lipid profile at baseline and after a six-month follow-up will be collected. This study was conducted to develop a dietary protocol (Diet4Hashi) that is easy to follow for HT subjects, and it will contribute to providing valuable data that are useful to dieticians and physicians. It is anticipated that this graphic–text qualitative dietary protocol, by improving food selection and diet quality, may reduce adiposity and improve metabolic parameters and the quality of life of HT women.

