### 2.11. Sample Size

The minimum sample size was calculated based on the expected improvement in overall QoL (decrease in points) and BMI (decrease in kg/m^2^) after the six-month follow-up and the expected difference between the experimental and the control group. A decrease in overall QoL and BMI with a 50% difference between groups (in the experimental/control group, a decrease by 20/10 points and 2.0/1.0 kg/m^2^, respectively) was assumed. For this calculation, a 5% significance level and 80% power were considered. The sample size required at baseline is approximately 100 respondents (for the experimental/control group: 50/50 for overall QoL and 42/42 for BMI), including a 20% drop-out rate at the end of the study. When the data collection is completed, the adequacy of the study sample will be checked by applying the post hoc statistics to calculate power.

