### 2.12. Statistical Analysis

Categorical variables will be presented as a sample percentage (%) and continuous variables will be presented as means with a 95% confidence interval (95%CI) or medians with an interquartile range (IQR) for variables with normal or non-normal distribution, respectively. To assess the impact of dietetic counseling and verify the differences between the experimental and the control group, two-tailed tests will be applied; *p*-values < 0.05 will be considered significant. 

The normality of variable distribution will be verified with a Kolmogorov–Smirnov test before the statistical analysis. For continuous variables, e.g., diet quality scores, AdhS, scores of QoL, nutrition knowledge score, TFTs, markers of adiposity, metabolic parameters, and changes after a six-month follow-up with respect to baseline will be verified with a T-test for dependent samples or a Mann–Whitney test, for variables with normal or non-normal distribution, respectively. For categorical variables, logistic regression modeling will be applied to determine the chance of the occurrence of high diet quality, high AdhS, high QoL, as well as low adiposity and elevated metabolic parameters. The odds ratios (ORs) and 95% confidence intervals (CIs) will be calculated. The significance of ORs will be verified with Wald’s statistics. A crude model and models with an adjustment for confounders will be created. All analyses will be performed with Statistica software (version 13.3 PL; StatSoft Inc., Tulsa, OK, USA; StatSoft, Krakow, Poland).

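### Section 2.12 tests every odds ratio with the Wald statistic alone, which at about 40 women per arm cannot reject when an arm has no events or only events and is conservative for uncommon outcomes

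*Protocol article*

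**What the plan says.** Section 2.12 (Statistical Analysis) states that "logistic regression modeling will be applied to determine the chance of the occurrence of high diet quality, high AdhS, high QoL", and also for low adiposity and elevated metabolic parameters. It continues "The odds ratios (ORs) and 95% confidence intervals (CIs) will be calculated" and "The significance of ORs will be verified with Wald’s statistics". Crude and confounder-adjusted models are both planned, and for group differences "two-tailed tests will be applied" with significance at p < 0.05. No likelihood-ratio, exact or penalised test is named for the odds ratios, and no method is given for their confidence intervals.

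Section 2.11 (Sample Size) bases the numbers on two continuous outcomes, overall quality of life and BMI: "a 5% significance level and 80% power were considered", giving baseline numbers "for the experimental/control group: 50/50 for overall QoL and 42/42 for BMI), including a 20% drop-out rate at the end of the study". It states no expected rate for any binary outcome.

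**The concern.** The hypothesis tested is OR = 1, but the Wald statistic takes its standard error at the fitted odds ratio, not at OR = 1. As one arm approaches 0% or 100%, that standard error eventually grows faster than the log odds ratio, so the statistic turns back towards zero. With an empty cell the estimate diverges, the standard error diverges faster, and software typically reports a Wald p-value near 1.

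This is a fixed rule and not an omission: an analysis plan that followed Section 2.12 would carry the Wald test forward. If a binary outcome were absent, or universal, in one arm, the written rule would call the comparison non-significant however large the contrast. The analyst would then have to report that, or change the test after seeing the data.

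**Working it through.** **Inputs**
- Women per arm at six months: 50 × (1 − 0.20) = 40 (Section 2.11). In reverse, 40 / 0.80 = 50, the plan's own figure for quality of life. The full sample-size calculation cannot be reproduced because no standard deviation is stated; this point does not need it.
- Two-sided 5% level (Sections 2.11 and 2.12).
- Outcome rates: not in the documents. All rates below are assumptions.

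**Formulas**, crude model, a/40 against b/40
- Wald: z = ln(OR) / √(1/a + 1/(40−a) + 1/b + 1/(40−b)). A table with 0/40 or 40/40 in an arm counts as non-significant.
- Firth: the log-likelihood plus half the log determinant of the information matrix. In this model the fitted rates are (a + 0.5)/41 and (b + 0.5)/41, and under OR = 1 the common rate is (a + b + 1)/82. Twice the difference in penalised log-likelihood is referred to chi-square with 1 df.
- Power and size: enumerate all 41 × 41 tables and weight each by its binomial probabilities.

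**Step 1: the Wald statistic turns back**, against 20/40
- 38/40: ln 19 = 2.944; SE = √(1/38 + 1/2 + 1/20 + 1/20) = 0.791; z = 3.72, p = 0.0002.
- 39/40: ln 39 = 3.664; SE = √(1/39 + 1/1 + 1/20 + 1/20) = 1.061; z = 3.45, p = 0.0006.
- 40/40: the SE contains 1/0. Wald p is about 1; Fisher p = 8 × 10⁻⁸.

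The statistic falls between 38/40 and 39/40 but stays far beyond 1.96. The verdict is lost only at the empty cell.

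**Step 2: an empty cell**, 0/40 against 10/40
- Wald: never significant. Fisher: p = 0.001.
- Firth: fitted rates 0.5/41 = 0.0122 and 10.5/41 = 0.2561; null rate 11/82 = 0.1341. Penalised log-likelihoods without the constant common to both are −26.03 and −32.32; statistic 2 × 6.30 = 12.6, p = 0.0004.

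**Step 3: how often an empty cell arises.** If the true rate in an arm is 2%, the chance is 0.98⁴⁰ = 44.6%. At 5% it is 0.95⁴⁰ = 12.9%.

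**Step 4: power**, 40 against 40

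| Assumed rates | Wald | Firth | Fisher |
|---|---|---|---|
| 20% v 2% | 27.4% | 78.6% | 64.4% |
| 20% v 5% | 32.5% | 54.0% | 41.1% |
| 25% v 5% | 55.3% | 74.8% | 64.6% |
| 40% v 15% | 71.7% | 72.3% | 64.1% |
| 50% v 25% | 64.7% | 64.7% | 55.9% |
| 60% v 30% | 79.6% | 79.6% | 72.5% |

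The mirrored high rates (for example 80% v 98%) give the same values.

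**Step 5: rejection rate under no effect**

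| Rate in both arms | Wald | Firth | Unpenalised likelihood ratio | Fisher |
|---|---|---|---|---|
| 5% | 0.0% | 3.8% | 9.1% | 0.4% |
| 10% | 1.2% | 4.5% | 6.5% | 1.7% |
| 20% | 4.1% | 5.1% | 5.2% | 2.8% |
| 50% | 5.7% | 5.7% | 5.7% | 3.3% |

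**Step 6: table by table.** Firth rejects every table that Wald rejects. Counting mirror-image arms once, the unpenalised likelihood-ratio test rejects 75 tables with an empty cell and Wald none of them. Without an empty cell, only 10 tables change verdict between those two tests, all borderline (Wald p 0.053 to 0.081), and Fisher is non-significant in each.

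**The case against.** The case against is substantial, and much of it stands.

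- **The failure is narrower than it may seem.** A reader might infer that Wald fails whenever nearly all or nearly no women have the outcome. It does not: 39/40 against 20/40 gives p = 0.0006. At 40% against 2%, Wald power is 55.1% overall, but 55.1 / (100 − 44.6) = 99.5% among trials without an empty cell.
- **No rates are given.** A reader might infer from the exclusion of diagnosed diabetes and cardiovascular disease (Table 2) that elevated metabolic parameters will be rare. The documents do not establish this. Women with BMI up to just under 35 are eligible, the cut-offs include total cholesterol ≥200 mg/dL and blood pressure ≥130/85 mmHg (Section 2.10), and the Introduction cites about 17% of Hashimoto patients with a fasting-glucose or glucose-tolerance abnormality. Nothing suggests that high diet quality will be near-universal.
- **Wald is a standard test.** Naming it is neither an error nor a contradiction, and Fisher's test is no general improvement. Without an empty cell, no table is significant by Fisher and not by Wald, while the reverse occurs.
- **An empty cell would be visible**, because the maximum-likelihood odds ratio does not exist, and handling of separation is often left to the analysis plan.

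The last argument does not dispose of the point. Visibility does not repair a rule that names one test, and changing tests after the data are seen is what pre-specification should avoid. The conservatism in Step 5 is also not confined to trials with an empty cell: at a 10% rate in both arms one occurs in only 2.9% of trials, yet Wald rejects 1.2%.

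**Conclusion.** The point holds as a minor one. Section 2.12 fixes a test that cannot reject at an empty cell and is conservative when outcomes are uncommon, where an alternative loses no rejections and kept its size at or below 5.7% at the rates checked. How much is lost rests on the assumed rates: about 21 points of power at 20% v 5%, about 51 at 20% v 2%, and next to nothing between about 20% and 80%. The figures are for crude models with 40 per arm; adjusted models were not computed.

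A reader might go further and infer that the second hypothesis, on quality of life, adiposity and metabolic parameters, could be answered wrongly. The documents do not support that: Section 2.12 also analyses these as continuous variables, and Section 2.11 sizes the trial on continuous quality of life and BMI. The point reaches only the supporting odds ratios compared between arms. It does not reach high AdhS, since the diaries behind that score are kept in the experimental arm only (Section 1.2 and Table 1), so no 40 v 40 comparison exists.

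**What to change.** Replace the Wald sentence in Section 2.12 with: *The significance of ORs will be verified with the penalised (Firth) likelihood-ratio test, with profile penalised-likelihood 95% CIs, in crude and adjusted models.*

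If only Statistica is available, use the likelihood-ratio test, and reserve Fisher's exact test for crude tables with an empty cell; applied more widely, Fisher would cost power for common outcomes (55.9% against 64.7% at 50% v 25%). State alongside that the unpenalised likelihood-ratio test is liberal for very rare outcomes (9.1% at a 5% rate).

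The cost is one sentence and no new data. The drawback is that the Firth fit may need software other than Statistica, the only package Section 2.12 names. Results for common outcomes would barely change.

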## 3. Discussion

The recommendations in the ‘Diet4Hashi’ protocol are based on scientific evidence related to Hashimoto thyroiditis and hypothyroidism, as described in detail in Section 3.1 and Section 3.2. They were also inspired by guidelines developed for the general population, including Polish guidelines as described in the Pyramid of Healthy Nutrition and Physical Activity [27].

### 3.1. Basis for Development of a Self-Monitoring Diary for Recommended Foods (A)

#### 3.1.1. Vegetables 

The consumption of vegetables is recommended several times a day, which is in line with the recommendation for the general population [27,28,29]. Various kinds of vegetables are recommended, although attention should be paid to the consumption of soybean-related foods and raw cruciferous vegetables (see Section 3.2). The special function of vegetables for HT subjects can be attributed to phytosteroles. These compounds are present in vegetables in moderate amounts and have shown immunomodulatory and anti-inflammatory properties [46]. 

#### 3.1.2. Foods Rich in Calcium

For foods rich in calcium (e.g., milk, fermented milk drinks, curd cheese, cheese), the recommended consumption frequency is several times a day, which is in line with the recommendation for the general population [27,28,29]. Calcium deficiencies can have serious consequences for the health of women with hypothyroidism. The main role of thyroid hormones is metabolism regulation, but it also participates in bone tissue reconstruction. One consequence of hypothyroidism is a reduction in the processes of bone tissue reconstruction resulting from the inhibition of bone mineralization. Therefore, the diet of patients with hypothyroidism should be rich in dietary calcium, such as milk, yoghurt, cheese, low-, regular-, or high-fat dairy, and small fish eaten along with bones [47]. Some studies on HT have focused on lactose intolerance diagnosed with an elimination diet, hydrogen tests, lactose tolerance tests, or small intestinal biopsies [16]. It was found that 75% out of 84 patients with HT, all of whom were residents of the Mediterranean Sea region and Turkey, had lactose intolerance. Asik et al. [48] found that lactose elimination from the diet of HT patients decreased the TSH level without a modification dose of levothyroxine. For this reason, the authors suggested that patients demonstrating great fluctuations in the concentration of TSH while taking a steady dose of levothyroxine should be tested for lactose intolerance.

#### 3.1.3. Fruits

Fruit consumption is recommended at least once a day, similar to the recommendation for the general population [27,28,29]. Fruits and vegetables are an abundant dietary source of polyphenols and micronutrients in the human diet (if consumed). They are known for their anti-inflammatory, immunomodulatory, and antioxidant effects in the body [49,50]. Tonstad et al. [51] reported an association of a vegan diet (rich in fruits and vegetables) and a lower risk of hypothyroidism. In 2014, a meta-analysis of 19 case-control studies on dietary factors and thyroid cancer risk found a weak inverse association with vegetable consumption and no association with fruit consumption [52]. 

#### 3.1.4. Whole Grains

The recommended consumption of whole grains, e.g., buckwheat grain, wholemeal wheat, and rye bread, at least once a day, is in line with the recommendation for the general population [27,28,29]. A gluten-free diet has been given a lot of attention with respect to HT. The literature shows that celiac disease is associated with an increased prevalence of autoimmune thyroid disease (AITD) and vice versa, with a prevalence of up to 9% of adults with AITD [53,54]. In celiac disease patients, the prevalence of hypothyroidism is 2% to 5% [55]. Krysiak et al. [17] suggest that a gluten-free diet may bring clinical benefits to subjects with autoimmune thyroid disease. The study included 34 Polish women with recently diagnosed and previously untreated AITD. Roy et al. [56] in a pooled analysis, including 6024 patients with AITD, found a markedly increased prevalence of biopsy-confirmed coeliac disease. The authors concluded that all patients with AITD should be screened for the presence of coeliac disease. Sategna et al. [57] observed that a gluten-free diet can reverse the abnormality of subclinical hypothyroidism, although they did not find a correlation between the time of exposure to gluten in celiac disease individuals and the risk of autoimmune diseases. Other authors also reported that a gluten-free diet has a protective effect against thyroid diseases, and they recommended that the gluten-free diet should begin early, before autoimmune disorders are established, in order to prevent or minimize their development [58]. To the contrary, Ch’ng et al. [53] disagreed with these findings, arguing that there is little evidence to support the use of a gluten-free diet to reduce the development of AITD. Following this data, a gluten-free diet is still controversial as to its effectiveness in preventing AITD and hypothyroidism. However, for the treatment of celiac disease, it is mandatory to follow a gluten-free diet [19,20,21]. Further investigation is necessary for a better understanding of the role of gluten in thyroid diseases. Currently, the recommendation for whole grains results from the content minerals, vitamins, and dietary fiber in these foods [27,28,29]. The consumption of whole grains can also improve selenium intake, e.g., whole-wheat flour contains 13.6 μg of selenium per 100 g (24.7% of recommended dietary allowance (RDA)) [27]. The average content of selenium in foods based on popular gluten-free cereals was 2.8 μg/100 g, and in foods based on oat, amaranth, teff, and quinoa, it was 10.8 μg/100 g [59].

#### 3.1.5. Animal Foods Rich in Zinc

The consumption of animal foods rich in zinc (e.g., meats and eggs) several times a week is recommended. This is in line with the recommendation for the general Polish population, who usually consume too much red and processed meats [60,61]. The RDA of zinc is 8 mg/day for Polish women, and this amount can be found in meats in amounts varying from 1.2 to 8.4 mg/100 g [28]. There are reports that zinc deficiency is one of the causes of subclinical hypothyroidism [62]. A previous study by Ertek et al. [63] suggested that zinc deficiency leads to a reduction in the level of FT4 and FT3 and the development of hypothyroidism symptoms. In humans, zinc supplementation brought the thyroid function back to normality in hypothyroidean patients. The majority of studies on zinc and the HT were focused on zinc supplementation, but these findings were not considered due to being out of the study aim [64,65,66]. 

#### 3.1.6. Animal Foods Rich in Selenium

The authors’ recommendation to consume animal and plant foods rich in selenium is in line with previous findings that diets rich in selenium may increase the production of active thyroid hormone and reduce TgAb and TPOAb [67,68,69]. Stoffaneller et al. [70] showed that selenium intake and selenium status was suboptimal in European and Middle Eastern countries, with lower levels in the Middle East. The highest selenium status of all studies in the European region was found in Poland, where boys had a mean serum selenium concentration of 111.1 μg/L (optimal level: 289.9 μg/L) [71,72]. Lower serum selenium levels were found in the patients with AITD (60–99 μg/L) [70]. The most recent meta-analysis found that the use of selenium supplements reduced serum TPOAb levels after 3, 6, and 12 months in HT patients treated with levothyroxine and after three months in untreated cases [73].

The authors have distinguished animal and plant dietary sources of selenium for three reasons: (i) to simplify recommendations for the patient, (ii) to reduce the chance of any unilateral exchange between both food groups and maintain a large variety of diet, and (iii) plant sources of selenium, i.e., nuts and seeds, are also rich in zinc.

Fish and seafood are indicated as animal foods rich in selenium with a recommended consumption of several times a week. This is in line with the recommendation for the general population, although a guideline on eating fish and seafood at least twice a week (including fatty fish at least once a week) is mainly based on the content of *n-3* polyunsaturated fatty acids in these foods [27,28,29]. Seafood and organic meats are good sources of selenium, followed by muscle meats [68,69]. 

#### 3.1.7. Nuts and Seeds

Various kinds of nuts and seeds are recommended to be consumed several times a week. These foods are a good source of selenium and zinc (both important in thyroid metabolism) and also rich in dietary fiber. Brazil nuts are the richest food source of selenium, although they cannot be recommended as a main selenium source because they are generally not a commonly eaten food, and selenium content is highly variable, ranging from 0.03 to 512 mg/kg fresh weight [68,74,75]. In general, in all kinds of nuts, the zinc concentration ranges from 2.1 to 4.7 mg/100 g [27,28,29]. Farhangi et al. [76] showed the potential beneficial effect of powdered seeds of *Nigella sativa* in improving thyroid status and anthropometric variables in patients with HT. Nevertheless, its function on the human thyroid requires more trials, and this finding should be interpreted with caution. The thyroid hormone is made by combining iodine and tyrosine. In a balanced diet, a person should receive enough of this amino acid, but tyrosine intake can be supported by the consumption of pumpkin seeds, sesame seeds, and almonds [27,28,29].

### 3.2. Basis for the Development of a Self-Monitoring Diary for Foods with Limited Consumption (B)

#### 3.2.1. Raw Cruciferous Vegetables

The consumption of raw cruciferous vegetables, e.g., kale, bok choy, white cabbage, red cabbage, broccoli, brussels sprouts, and cauliflower should be limited (once a week or less). Cruciferous vegetables, as well as soybean-related foods, contain goitrogens, which interfere with thyroid hormone production and utilization. A goiter may be a response to an overactive or underactive thyroid gland. Unless there is a co-existing iodine deficiency, these foods are generally of no clinical significance according to the statement of the Institute of Medicine [77]. Goitrogens are inactivated by heating and cooking—the thermal processing leads to inactivation of about 30% of goitrogens. [77]. Thus, it is important to educate patients on how to prepare these vegetables. Matana et al. [23] showed that a dietary group with a higher consumption of root vegetables, flower vegetables, leafy vegetables, fruity vegetables, and legumes was negatively associated with plasma TP-Ab and/or TgAb (upper tertile OR = 0.88, 95% CI 0.78–0.99 versus bottom tertile, *p* = 0.048).

